### Ethical Considerations

Ethics approval has been obtained from the institutional review board of LRH, Peshawar (application reference: 399/LRH/MTI). All participants will provide written informed consent. All data will be deidentified prior to analysis. Data will be stored on encrypted institutional servers accessible only to named study personnel. No financial compensation will be provided to participants.

## Results

### Overview

This study received no external funding. As of manuscript submission, participant recruitment has not yet commenced because pilot deployment is scheduled to begin in June 2026. System development, stakeholder engagement, user-centered design, beta testing, and validation activities have been completed. Data collection is expected to continue through November 2026, quantitative and qualitative data analysis is planned for December 2026 through February 2027, and study findings are expected to be submitted for peer-reviewed publication in spring 2027. System development, user-centered iterative design, stakeholder engagement, beta testing, and validation have been completed. The pilot implementation phase is scheduled to commence in June 2026 across a phased sequence of participating facilities beginning with primary and secondary care hospitals and expanding to the 3 tertiary MTIs by July 2026. Data collection will continue for a 6-month period, with an anticipated sample of 5000 to 7000 emergency referral records. Qualitative data collection will begin at approximately 2 months following platform deployment and will continue until November 2026. Quantitative and qualitative data analysis is planned for December 2026 to February 2027.

### Study Timeline

The study timeline is outlined in Table 3.

**Table 3 table3:** Study timeline.

Phase and activity	Time frame	Status
Phase 1: requirement gathering and stakeholder consultation	January 2026-February 2026	Completed
Phase 1: platform design, prototyping, and development	February 2026-May 2026	Completed
Phase 1: beta testing and iterative refinement	May 2026	Completed
Phase 1: validation testing and health care professional training	May 2026	Completed
Phase 2: pilot deployment and data collection—primary and secondary care facilities	June 2026-August 2026	Planned
Phase 2: pilot deployment and data collection—tertiary MTIs^a^	July 2026-November 2026	Planned
Phase 2: qualitative data collection (surveys, interviews, and focus groups)	August 2026-November 2026	Planned
Phase 3: data analysis (quantitative and qualitative)	December 2026-February 2027	Planned
Phase 3: report preparation and policy dissemination	March 2027-April 2027	Planned

^a^MTI: Medical Teaching Institution.

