## Methods

### Study Design

This is a mixed methods implementation study with a prospective cohort design for the quantitative component and a qualitative exploratory component. The quantitative component captures all emergency referrals recorded through the digital platform during a defined 6-month pilot period using preimplementation historical referral data from participating institutions for pretest-posttest comparison. The qualitative component examines health care provider and patient experiences through surveys, semistructured interviews, and focus group discussions. Quantitative and qualitative findings will be integrated using a convergent mixed methods framework.

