### Data Collection

Quantitative data will be collected automatically by the digital platform, recording referral time stamps, referral reason, urgency category, facility identifiers, bed availability status, and referral outcome. Preimplementation historical data will be extracted from paper registers at participating institutions. Health care professional surveys will be administered at 2 time points: within 2 weeks of deployment and at the end of the 6-month period. Patient surveys will be administered at the point of referral completion. Semistructured interviews will be conducted at midimplementation and at end of study. Focus group discussions will be held at approximately 3 months after deployment. Data quality will be checked through double-entry verification of a random 10% sample and monthly data monitoring committee reviews.

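### The first provider survey is due within 2 weeks of deployment, but Table 3 opens surveys in August 2026, too late for every site that goes live in June

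*Protocol article*

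**What the plan says.** Three places in the protocol article fix the timing of the provider survey.

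- **Methods, Data Collection:** "Health care professional surveys will be administered at 2 time points: within 2 weeks of deployment and at the end of the 6-month period".
- **Results, Overview:** "pilot deployment is scheduled to begin in June 2026", in a phased sequence "beginning with primary and secondary care hospitals and expanding to the 3 tertiary MTIs by July 2026". The same paragraph states: "Qualitative data collection will begin at approximately 2 months following platform deployment and will continue until November 2026".
- **Results, Study Timeline, Table 3:** the row "Phase 2: qualitative data collection (surveys, interviews, and focus groups" is dated August to November 2026. No other row schedules a survey.

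Surveys count as part of the qualitative strand. The Study Design section says: "The qualitative component examines health care provider and patient experiences through surveys, semistructured interviews, and focus group discussions". In the Outcomes section and Table 2, provider satisfaction and usability is a secondary outcome, its data source is the structured survey, and it is to be summarised by means and SDs and integrated with the themes.

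**The concern.** The Methods instruction and the timeline give different start dates for the same activity. A wave due within 14 days of a June deployment cannot be collected in a window that opens in August. The Table 3 date does not look like a slip, because the overview gives the same delay in words.

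The first wave is the only planned provider measurement close to go-live. If field staff work from the timeline, providers at the June sites will already have had the platform for at least a month when first asked. Responses from the first two weeks cannot be collected afterwards. The secondary outcome would then have its end-of-period measurement as planned, but not its early one.

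**Working it through.** **Inputs**

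- Limit for provider wave 1: 14 days after deployment (Data Collection).
- Go-live at primary and secondary facilities: June 2026 (Overview, Table 3).
- Go-live at tertiary institutions: July 2026 (Table 3; the Overview says by July).
- Earliest survey date under the timeline: 1 August 2026, the first day of the August to November row.
- Assumption: the article gives months without days, so I take the first and last day of each month as the range.

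**Formulas**

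- Window closes = go-live + 14 days.
- Delay = 1 August − go-live.
- Overrun = delay − 14 days. A negative value means that part of the window falls in August.

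**Results**

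| Go-live | Window closes | Delay to 1 August | Overrun |
|---|---|---|---|
| 1 June (earliest, primary and secondary) | 15 June | 61 days | 61 − 14 = 47 days |
| 30 June (latest in June) | 14 July | 32 days | 32 − 14 = 18 days |
| 1 July (earliest in July, tertiary) | 15 July | 31 days | 31 − 14 = 17 days |
| 31 July (latest in July) | 14 August | 1 day | 1 − 14 = −13 days |

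**June sites.** The overrun is positive across the whole month, so no June go-live date satisfies both schedules. These figures use the first day that the row allows, and any later August start lengthens the delay.

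**Tertiary sites.** The break-even go-live is 1 August − 14 days = 18 July. With deployment read per facility, a site going live on or after 18 July can be surveyed on time in August, and a site going live earlier cannot. The article does not say whether deployment means each facility's go-live or the single platform launch. If it means the June launch, the June rows of the table apply to every provider.

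**Other activities in the same row.** The Data Collection section places focus groups at about 3 months and interviews at mid-implementation and at the end of the study. With a June start these fit August to November. Provider wave 2, at the end of a 6-month period that starts in June, falls in November and also fits. Provider wave 1 is the provider activity that does not.

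**A related date.** Table 3 ends the deployment and data collection row for primary and secondary facilities in August 2026. The Overview says that collection continues for 6 months. As the table stands, wave 2 in November would fall outside the listed window for those facilities.

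**The case against.** The strongest reply is that a specific Methods instruction outranks a summary timeline. Staff who follow the Data Collection section would run wave 1 on time and nothing would be lost. In addition, the overview sentence mentions neither surveys nor August, so only Table 3 states the later survey date directly. Both observations are accurate, and the loss does depend on which text is followed. But nothing in the article says which one governs. Table 3 names surveys explicitly, and the Study Design section places them in the strand that the overview delays. The conflict therefore stands for the June sites.

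A reader might infer more than this, and four stronger readings are not supported.

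- **That the tertiary sites certainly miss the first wave.** No go-live day is given. With deployment read per facility, a go-live on or after 18 July removes the conflict.
- **That a planned comparison between waves is undermined.** Table 2 lists no such test for the provider survey. The paired comparisons in the Data Analysis section are stated generally and do not name it.
- **That patient surveys wrongly lose June and July.** The instruction to survey patients when a referral is completed sets the point in the patient's pathway, not the calendar start. Patients are a convenience sample, and coverage of every month is not promised.
- **That the August responses would reflect established use.** The article sets no threshold between early and established use. What can be said is that they would fall outside the stated 2-week window.

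**Conclusion.** The concern holds for primary and secondary facilities going live in June 2026. The earliest survey that Table 3 allows falls 32 to 61 days after go-live, 18 to 47 days beyond the stated limit, and this is so for every possible June date. For tertiary institutions it holds only for a go-live before 18 July, with deployment read per facility.

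The consequence is limited but real. If the timeline is followed, the planned early wave of a secondary outcome is lost as specified at the June sites and cannot be recovered. What suffers is the description of provider satisfaction and usability at two time points. No hypothesis test is affected, and neither primary outcome depends on the survey.

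The conclusion rests on the stated months, on 1 August as the earliest date in the row, and on surveys belonging to the qualitative strand, as Table 3 and the Study Design section both say.

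**What to change.** Before go-live:

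1. Give surveys their own row in Table 3. Put provider wave 1 within 2 weeks of each facility's go-live, from June 2026, and wave 2 at the end of the 6-month period. Say in the Data Collection section that deployment means the facility's own go-live.
2. Leave interviews and focus groups in the August to November row.
3. Limit the overview sentence on the 2-month start to interviews and focus groups, so that it matches.
4. Reconcile the primary and secondary row that ends in August 2026 with the 6-month collection period, so that wave 2 at those facilities falls inside their listed window.

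Starting patient surveys at go-live would also be sensible, to cover the start-up months. That is an improvement rather than a correction.

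The cost is small: an edit to one table and two sentences. The survey instrument already exists as Multimedia Appendix 1, and the analysis does not change. The practical demand is that the first wave must be ready to run at the June sites when they go live.

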## Discussion

### Principal Findings

This protocol describes the design, development, and planned evaluation of a neurosurgery-led digital emergency referral system in KP, Pakistan. It is anticipated that the study will show that a structured mobile- and web-based referral platform may decrease the rate of unnecessary emergency transfers, decrease the time spent on initiating a referral and responding to it, and enhance bed occupancy rates in tertiary care facilities.

### Comparison With Prior Work

This research is based on the accumulating evidence on digital referral systems in LMICs, such as the Mobile Obstetric Referral Emergency System in Liberia [8], the Saudi Medical Appointments and Referrals Centre in Saudi Arabia [9], web-based neurosurgical referral systems in higher-income countries [10], and evidence from Indonesia [11] and systematic reviews on e-referral solutions [12].

### Strengths and Limitations

The strengths are a multicenter design with all levels of health care, high expected volume of samples, and the combination of quantitative and qualitative approaches. Limitations are the lack of randomization, the digital literacy and connectivity differences between facilities, the possible incompleteness of preimplementation paper records, and operational pressures that can influence study compliance.

### Future Directions

Future directions could include provincial scale-up, interoperability with the National Database and Registration Authority in Pakistan, artificial intelligence–assisted triage, and economic assessment.

The results of the study will be shared with the KP Health Department and the MTI administrations through peer-reviewed publications, conference presentations, and formal reports. Open access publication will be given priority.

### Conclusions

This protocol describes a stringent mixed methods implementation study of a neurosurgery-based digital emergency referral platform in KP, Pakistan. The results can be used to offer a transferable evidence base to justify the use of digital referral systems in KP and similar LMIC contexts.

## Data Availability

Deidentified data generated during this study may be made available from the corresponding author on reasonable request subject to institutional approvals, ethics approval conditions, and applicable data protection requirements.

## Appendix

Multimedia Appendix 1 Health care provider and patient survey instruments for the evaluation of the KP MTI referral app.

Multimedia Appendix 2 Semistructured interview and focus group discussion topic guides.

## Abbreviations

HMC: Hayatabad Medical Complex
KP: Khyber Pakhtunkhwa
KTH: Khyber Teaching Hospital
LMIC: low- and middle-income country
LRH: Lady Reading Hospital
MTI: Medical Teaching Institution
